# Gut inflammation

|                                                                                                      |     |
|------------------------------------------------------------------------------------------------------|-----|
| Standard deviation of gut inflammatory markers in controls                                           | 1   |
| Expected Mean difference between groups                                                              | 0.5 |
| Effect size                                                                                          | 0.5 |
| Alpha error (%)                                                                                      | 5   |
| Power (1- beta) %                                                                                    | 90  |
| 1 or 2 sided                                                                                         | 2   |
| Required sample size per group                                                                       | 84  |
| Total sample size required                                                                           | 168 |
| Total sample size approved for the study including attrition                                         | 250 |
| Sample size may be revised after first 100 assays after reviewing the mean and SD of the gut markers |     |

Stool will be collected from 400 infants at baseline and at 1 month age (ethics approval obtained) from those who provide consent. After the first 100 assays an independent DSMB can look at the data and guide if sample size revision for the gut inflammatory markers are required.

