## **Hypotheses**

In LBW infants, c-KMC leads to:

1. Improved infant breast milk intake (at least 60 ml increase);
2. Substantial reduction in the prevalence of postpartum moderate to severe depressive symptoms (prevalence ratio  $\leq 0.7$ ) and substantial reduction in salivary cortisol levels (reduction of at least 0.3 SD in mean values) as a marker of maternal stress.
3. Reduction of gut inflammatory markers -Fecal Neopterin, Myeloperoxidase, alpha1antitrypsin (reduction of at least 0.5 SD in mean values)

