## **Objectives**

### **Primary Objectives (for the PhD thesis):**

To estimate the effect of community initiated Kangaroo mother care during the neonatal period in LBW infants on:

1. Infant breast milk intake during neonatal period

2. Prevalence of moderate to severe postpartum depressive symptoms (Patient Health Questionnaire-9 score  $\geq 10$ ) and stress (measured by salivary cortisol levels) at the end of the neonatal period
3. Gut inflammation as reflected in levels of fecal neopterin, myeloperoxidase,  $\alpha 1$  antitrypsin at the end of the neonatal period.

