### **Description of the PhD sub-study**

*Sample sizes for the sub-study (Vide Annexure 3):*

With 95% confidence and 90% power and expecting approximately 10% attrition, a total sample size of:

- 550 mother-infant dyads (275 in each group), will be sufficient to detect a 0.3 SD, i.e. 60ml, increase in infant breast milk intake with 90% power (1SD = 200ml),
- 1950 mother-infant dyads (975 in each group) will be sufficient to detect a 30% relative reduction in the prevalence of moderate to severe postpartum depressive symptoms (PHQ 9  $\geq 10$ ), assuming a baseline prevalence of 19%,
- 550 mothers will be sufficient to detect a 0.3 SD i.e. 1.5 ug/dl decrease in the mean saliva cortisol levels (biomarker of stress),
- 250 infants (125 in each group) will be sufficient to detect a 0.5 SD reduction in the levels of gut inflammatory markers.

Therefore, the overall sample size will be 1950 mother infant dyads in whom the prevalence of postpartum depressive symptoms will be assessed using PHQ 9. Infant breast milk intake, and salivary cortisol (biomarker of stress) will be assessed in a sub-sample of 550 subjects; Infant gut inflammatory markers will be assessed in 250 subjects. Information on the linear growth-related outcomes and possible serious bacterial infection will be available for all these study subjects. The secondary outcomes related to breastfeeding i.e. lactation failure, perceived milk insufficiency, breastfeeding performance will be measured in the sub-sample of 550 subjects.

*Inclusion and Exclusion:* Singleton Low birth weight babies ( $\geq 1500$  to  $\leq 2250$  g) aged  $>72$  hours to 7 days who are either born at home or hospital but KMC not initiated in the hospital and are already a part of the trial titled “Effect of Community Initiated Kangaroo mother care on babies with Low Birth Weight” will be included in this sub-study.

In the sub-study, we will exclude infants whose mother expired or is not living with the baby for any reason. Also for the subsample of the 550 mothers where infant breast milk intake will be assessed, twins or triplets (~5% of the total LBW births) will be excluded because of the difficulties involved in accurately assessing breast milk output in mothers with twins/ triplets using the deuterium oxide method.

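### Three primary gut markers have no stated success rule or multiplicity control, and the 100-assay sample-size review does not fit its own 0.5 SD target

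*Combined protocol and SAP*

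**What the plan says.** The third primary objective is "Gut inflammation as reflected in levels of fecal neopterin, myeloperoxidase" and alpha-1-antitrypsin; the list of primary outcomes repeats the three markers. The Hypotheses section gives the expected effect for them as "reduction of at least 0.5 SD in mean values".

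Annexure 3 (Gut inflammation) has a single calculation. The row "Standard deviation of gut inflammatory markers in controls" is 1 and the row "Expected Mean difference between groups" is 0.5, with two-sided alpha 5% and power 90%. The result is 84 per group, 168 in total, with 250 approved after attrition. The sub-study description says "250 infants (125 in each group) will be sufficient to detect a 0.5 SD reduction in the levels of gut inflammatory markers", in a list introduced by "expecting approximately 10% attrition".

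On the review, the same table says "Sample size may be revised after first 100 assays after reviewing the mean and SD of the gut markers". The note below it adds "After the first 100 assays an independent DSMB can look at the data and guide if sample size revision" is needed, and that stool will be collected from 400 infants.

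The Data analysis paragraphs plan unpaired t-tests or Mann-Whitney tests, then linear regression. They mention neither multiplicity nor an interim look. The only SAP supplied covers depressive symptoms and cortisol.

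**The concern.** Two things are missing.

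First, three primary markers are each tested at 5% with no statement of what counts as success. If a reduction in any one may be reported as an effect on gut inflammation, the chance of a false claim is well above 5%.

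Second, the sample-size review is not tied to anything it could properly change. The target is standardised, so the SD drops out of the calculation. No revision rule, cap or blinding status is given, and no adjustment of the final test. A reader of the results could not tell whether the final number of infants was set independently of the observed effect.

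**Working it through.** **1. The plan's own figure.** Inputs from Annexure 3: difference 0.5, SD 1, two-sided alpha 5%, power 90%.

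n per group = 2(1.960 + 1.2816)² / 0.5² = 84.06. The stated 84 is reproduced (85 if rounded up). A one-sided 5% test would need only 69, so the figure is indeed two-sided.

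**2. Multiplicity, if any one marker suffices.** For three independent tests, 1 − 0.95³ = 14.3%. By simulation of equally correlated normal statistics (the correlations are assumptions; the documents give none):

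| Correlation | Family-wise error |
|---|---|
| 0 | 14.3% |
| 0.3 | 13.6% |
| 0.5 | 12.5% |
| 0.7 | 10.9% |
| 0.9 | 8.3% |

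**3. If all three must succeed.** No alpha split is needed, but power falls. At 84 per arm it is 0.90³ = 73% for independent markers. At 112 per arm, where each 5% test has 96.1%, it is 0.961³ = 89%.

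**4. Cost of an alpha split.** At two-sided 0.05/3, z = 2.394 and n = 2(2.394 + 1.2816)² / 0.25 = 108.1, so 109 per arm or 218 evaluable. Enrolment is 218/0.90 = 243 at 10% attrition and 218/0.85 = 257 at 15%. Power per marker at alpha/3 (t-test, 0.5 SD) with 250 enrolled:

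| Evaluable per arm | Basis | Power |
|---|---|---|
| 112 | 10% attrition | 90.7% |
| 106 | 15% attrition | 88.9% |
| 84 | the table's requirement | 79.3% |

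The last row matters because 1 − 168/250 = 32.8%: going from 168 to 250 implies about 33% attrition. At 10%, 168 would inflate only to 187.

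**5. What the review can change.** With the difference fixed at 0.5 SD, the SD cancels: rounded up, n is 85 per group for an SD of 0.5, 1, 2 or 5. The SD matters only for an absolute difference. For a fixed 0.5 units, an SD of 0.8 gives 54, 1.2 gives 122 and 1.5 gives 190 per group.

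**6. If by-arm means drove the revision.** Assumptions, not in the documents: review at 50 per arm, cap of 200 per arm (half of the 400 stool donors), n recalculated from the observed difference, and an unadjusted final z-test at 5%. Type I error per marker is then:

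- 5.5% if n may only rise from 125 per arm;
- 5.9% if it may only rise from 84;
- 6.1% if it may also fall, as far as 50.

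If 100 assays meant 25 infants per arm, because each infant gives two stools, the corresponding range is 5.4% to 6.7%. A review of pooled means and SDs would cause little or no inflation.

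**The case against.** **The review may be benign.** Because neither the SD nor a pooled mean can alter n under a 0.5 SD target, a reader might infer that the review must be an unblinded, effect-driven change of size. The documents do not say so. They do not describe the means as by arm, and an independent board does the looking. The breast-milk and cortisol tables in Annexure 3 also size from a level mean and an SD: about 10% of 600 ml with SD 200, and about 20% of 7 ug/dl with SD 5. The gut table's unit SD could be a placeholder awaiting the same two inputs, which would make this an ordinary nuisance-parameter review. That stands as a possible reading. It does not remove the mismatch with the 0.5 SD target, or the absence of a rule. The breast-milk review described in the Methods refers to SDs only, so the mean is a real addition here.

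**The interim figures are conditional.** The split of 50 per group is stated for breast milk, not for stool. A figure near 10% (9.9%) can be produced, but only with a rule chosen to maximise error and free to stop at 50 per arm. Nothing in the plan proposes that.

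**The hypothesis can be read jointly.** The Hypotheses section speaks of reducing the three markers together, and the objective is to estimate. If all three were required, no correction would be due. This stands, and it is why the missing success rule comes first.

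**A gut SAP may exist.** The SAP supplied serves one of three planned papers. The supportable claim is that these documents state no error control, not that none exists.

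**Conclusion.** The point holds in this form. The 84 per group is correct. What is missing is a success rule, a multiplicity rule and a definition of the review.

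Multiplicity is the larger issue: about 11-14% family-wise error if any marker suffices and correlations lie between 0 and 0.7. The review is the smaller one: about half to one percentage point per marker if by-arm differences drive n under the assumptions above, and little or nothing if the review is pooled. The documents do not settle which applies.

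One might also infer that correction is free because 250 exceeds 168. That holds narrowly, for a t-test at 10% attrition, where the margin over 90% is under one point. It fails at 15% attrition. With a Mann-Whitney test at an assumed relative efficiency of 0.955, 112 per arm gives about 89%.

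**What to change.** 1. State the success rule for the gut objective. If any single marker can support the claim, test the three with Holm, and restate that 250 infants give about 91% power per marker at the first step (alpha/3) with 112 evaluable per arm. If all three are required, say so and report the joint power.
2. State the attrition assumed for stool outcomes and reconcile it with the step from 168 to 250.
3. Limit the 100-assay review to arm-blind pooled quantities: assay failures, values below detection limits and pooled SD. Say whether 100 assays means 100 infants with day-28 results. Allow the size to change only against a target restated beforehand as an absolute difference, for example on the log scale, with a cap.
4. If the review has already taken place, report what was seen, by whom, whether by arm, and what was decided.

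The cost is wording, plus some power. Under Holm, the first-step power falls below the planned 90% to about 89% at 15% attrition, and to about 79% if only 84 per arm are evaluable. No extra infants are needed at 10% attrition; at 15%, keeping 90% would take 257 rather than 250.

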**Annexure 4. Table showing schedule of anthropometry / collection of biological specimen**

| Outcome measured                | Sample/Procedure     | Method                   | Total Sample | Day enrolment | Day 1 | Day 3 | Day 7 | Day 13 | Day14 | Day 28 (age) |
|---------------------------------|----------------------|--------------------------|--------------|---------------|-------|-------|-------|--------|-------|--------------|
| Infant Breast milk intake       | Saliva-Mother Infant | FITR  /ELISA | 550          | √             | √     | √     | √     | √      | √     | -            |
| Depressive symptoms             | PHQ-9 (Mother)       | Questionnaire            | 1250         | -             | -     | -     | -     | -      | -     | √            |
| Stress (Cortisol)               | Saliva-Mother Infant | ELISA                    | 550          | -             | -     | -     | -     | -      | -     | √            |
| Gut inflammation                | Stool (5g)           | ELISA                    | 250          | √             | -     | -     | -     | -      | -     | √            |
| Successful BF/Lactation failure | BF assessment        | Questionnaire            | 550          | -             | -     | -     | -     | -      | -     | √            |

The days indicates days after enrolment in the KMC substudy (PhD) unless indicated otherwise

The first four parameters are the primary objectives of the PhD; and the last three parameters are not necessarily a part the PhD

Fourier transform infrared spectrophotometry

## **Annexure 5. Other outputs of this research work**

### **A. Other Objectives of this Research (not necessarily a part of the PhD)**

1. To assess the effect of c-KMC on:
  - a. Infant gut microbial composition and relative abundance of *Bifidobacterium* at the end of neonatal period
  - b. Linear growth velocity and attained length for age Z (LAZ) scores and the prevalence of stunting in the first 6 months of life.
  - c. Cumulative incidence of possible serious bacterial infection (PSBI) during the neonatal period and;
  - d. Skin maturation assessed through neonatal skin score
2. To study the association between infant milk intake with linear growth and incidence of PSBI
3. To study the association between maternal body composition (% body fat, fat mass and fat free mass) on infant birth weight, breast milk intake and linear growth

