##### Participants

Mothers and low birth weight infants ( $\geq 1500$  g to  $\leq 2250$  g) enrolled within 72 hours of birth

- Identified at home by surveillance team, either born at home or discharged from hospital without KMC having been initiated.

*Please state the reason(s) for the choice of patient group(s)*

The selected participants (babies with birth weight ranging from 1500 to 2250 g) and their mothers represent the target group for the intervention.

☒ Minors

☒ Under 12 years of age

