**Exclusion criteria**

- Birth weight <1500 g
  - Twins and triplets
  - Confirmed inability to feed
  - Major congenital malformations
  - Infant with breathing problems or abnormally inactive
  - Mother does not intend to stay in the study area for the next 6 months
  - Mother expired
  - Mother not living with the baby
- 

|                                              |
|----------------------------------------------|
| 3.2 Consent has already been obtained |
|----------------------------------------------|

|                                   |     |
|-----------------------------------|-----|
| Consent has already been obtained | Yes |
|-----------------------------------|-----|

---

*For which participants, information and any possible samples has consent already been obtained?*

All participants consented for participation and specimen collection.

---

*Which body approved the previous information material?*

Ethics Review Committee of the Society for Applied studies.

Main study "Impact of Promoting Kangaroo Mother Care (KMC) for Low Birth Weight Infants" (2015/1486) approved by REC.

---

|                                                                                        |
|----------------------------------------------------------------------------------------|
| 3.3 An application is made for exemption from the requirement to obtain consent |
|----------------------------------------------------------------------------------------|

|                                                                             |    |
|-----------------------------------------------------------------------------|----|
| An application is made for exemption from the requirement to obtain consent | No |
|-----------------------------------------------------------------------------|----|

---

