## Introduction:

Globally, Low birth weight (LBW) babies (<2500 grams) constitute 15% of all live births(1). India accounts for more than 40% of all LBW babies globally with 7.5 million babies (or 20% of the country's live births) being born with LBW(2). These babies have a reduced survival probability and contribute to 60-80% of the overall neonatal mortality(2). The key determinants underlying high mortality in these children are hypothesized to be infections and poor nutrition. Therefore, promotion of better nutrition and control of infections in these babies is essential to reduce neonatal mortality.

KMC is endorsed by the World Health Organization (WHO) for increasing the survival and well-being of LBW infants, particularly those born with a weight less than 2000 grams. The key components include early and prolonged skin-to-skin contact (SSC) between the mother and baby along with exclusive breast feeding(EBF) (3). The evidence for its mortality reduction is from hospital-based trials, mostly in developed countries (4). But the potential pathways through which KMC reduces mortality remain largely unclear. A large impact of neonatal mortality in LBW babies is plausible and may be mediated through several pathways driven through SSC; better mother-infant bonding, and protection conferred by breast milk. In addition to the documented effect of improved thermoregulation, the plausible pathways through which KMC operate may be reduced pathogen exposure and thereby prevention of infections, improvements in breast milk quantity and quality through reduced maternal stress, thereby promoting better nutrition and growth, early establishment of successful breastfeeding, better skin barrier, reduction in gut inflammation and establishment of a gut microbiome rich in *Bifidobacteria* and with fewer pathogenic bacteria. In a large ongoing trial, investigators of Society for Applied Studies, New Delhi, India, are examining the effect of c-KMC on neonatal and infant mortality, possible serious bacterial infection and linear growth. This PhD research aims to build in mechanistic sub-studies within this large trial to assess the effect of c-KMC on infant breast milk intake and breastfeeding performance; maternal postpartum depressive symptoms and stress; infant gut inflammation which are important biological outcomes related to growth promotion and infection prevention.

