## Methods

### **Brief description of the main trial** (in which this research will be embedded)

To answer the objectives of this research, a sub-study will be embedded in the large ongoing individually randomized controlled trial entitled “*Impact of Community-initiated Kangaroo Mother Care on Survival of Low Birth Weight Infants*” ([www.clinicaltrials.gov](https://www.clinicaltrials.gov/ct2/show/study?term=NCT02653534&rank=1) #NCT02653534) where 10,500 LBW infants will be enrolled to examine the impact of community initiated KMC on neonatal and infant mortality(6).The identification, screening and enrolment of mother-infant dyads for this sub-study will be embedded within the main trial.

*Setting:* The trial is being conducted in the rural and semi-urban areas of districts of Faridabad and Palwal in the state of Haryana (India), with a population of ~2 million, annual birth rate of 25.6/1000 population with around 20% of the babies being born with LBW.

*Population:* The study population comprises of mother infant dyads with babies weighing  $\geq 1500$  g to  $\leq 2250$  g enrolled within 3 days of birth identified by the study surveillance teams, either born at home or discharged from hospital and for whom KMC was not initiated in the hospital.

*Inclusion and exclusion criteria:* Infants unable to feed, with breathing problems, major congenital malformations or less active on the day of visit are referred to hospitals. Those intending to move away over the next 6 months or refuse participation are also excluded.

*Screening, enrolment and randomization:* In the main trial, pregnant women are being identified and followed up, their babies are weighed at birth and enrolled if eligible by study workers. Additionally, infants who are ill or whose weight is  $< 1800$ g are counseled to visit health facilities as mandated by government. However contact is maintained with such families and they are screened for enrolment when discharged from hospital if still within the 3 day enrolment window. Eligible infants are randomized using a randomization list prepared by an offsite statistician from WHO not otherwise involved with the trial. Allocation of subject IDs is done using serially numbered opaque sealed envelopes. At baseline, following consent, a questionnaire is administered to obtain sociodemographic details and child anthropometry is done.

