### **B. Tentative titles of other Possible papers that can emerge from this research (not necessarily a part of the PhD- may be included if required)**

1. The effect of c-KMC on gut microbial composition in LBW infants in India.
2. Association between maternal postpartum depressive symptoms and stress on infant breast milk intake
3. Association between maternal postpartum depressive symptoms and stress on linear growth
4. Association between gut microbial composition of LBW neonates in which half have received c-KMC and their linear growth in the first six months of life.
5. Effect of c-KMC on neonatal skin condition in LBW infants
6. Association of maternal body composition with infant birth weight, breast milk intake and linear growth (from secondary data that will be generated from this work).

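### Annexure 5 relates maternal body composition to birth weight in infants enrolled only at 1500–2250 g, so the linear-regression slope is biased towards zero relative to all births

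*Combined protocol and SAP*

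**What the plan says.** Annexure 5 A, which lists research outside the core PhD, gives as its third objective "To study the association between maternal body composition (% body fat, fat mass and fat free mass) on infant birth weight, breast milk intake", followed by linear growth. Annexure 5 B lists a matching tentative paper, "Association of maternal body composition with infant birth weight, breast milk intake and linear growth", to be written "from secondary data that will be generated from this work".

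Eligibility is set on birth weight. Section 2.4.2 of the ethics application states "The selected participants (babies with birth weight ranging from 1500 to 2250 g) and their mothers represent the target group for the intervention". The exclusion criteria in section 3.1 include "Birth weight <1500 g". The same 1500 to 2250 g window appears in the main-trial description and in the sub-study's own inclusion paragraph.

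No normal-weight comparison group is described. The protocol's Data analysis section names multivariable linear regression as the general tool for quantitative outcomes and gives no model for this objective. The SAP covers depressive symptoms and cortisol only. Neither document mentions range restriction, a truncated-outcome model, or a target population for this association.

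**The concern.** In the birth-weight part of this objective, the sample is chosen by the value of the outcome. Linear regression assumes that the error around the fitted line is unrelated to the predictor. When infants below 1500 g and above 2250 g are removed, the errors that can survive depend on the predicted value, and the fitted slope is pulled towards zero. A larger sample does not remove this. Covariate adjustment does not remove it either, because selection acts on the outcome itself.

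At stake is how one secondary paper would be read. A small slope could be taken to mean that maternal fat or lean mass has little bearing on birth weight, when the inclusion window would produce a small slope even under a real relation. The milk-intake and growth parts of the objective do not have birth weight as their outcome, so the calculation below does not apply to them.

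**Working it through.** The documents give no sample size, effect size or power for this objective, so there is no stated figure to reproduce.

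**Inputs from the documents**
- Selection window: 1500 to 2250 g (section 2.4.2; exclusion criteria).
- Low birth weight cut-off: "Low birth weight (LBW) babies (<2500 grams" (protocol Introduction).
- Share of low birth weight in the study area: "with around 20% of the babies being born with LBW" (main-trial description, Setting).
- Illustrative numbers of mothers: 550 approved, 468 required (Annexure 3, breast milk intake). Neither is stated for this objective.

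**Inputs assumed**
- Birth weight is normal in the source population, with an SD of 350 to 600 g (450 g central).
- The mean is set so that 20% fall below 2500 g: mean = 2500 + 0.8416 × SD.

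**Step 1: variance left in the window.** Let a = (1500 − mean)/SD, b = (2250 − mean)/SD and Z = Φ(b) − Φ(a). The ratio of the variance inside the window to that of all births is

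k = 1 + [aφ(a) − bφ(b)]/Z − {[φ(a) − φ(b)]/Z}².

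At SD 450 g: mean = 2879 g, a = −3.064, b = −1.397, Z = 0.080. Then k = 1 + 2.483 − (−1.831)² = 0.129. The SD inside the window is 450 × √0.129 ≈ 162 g.

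**Step 2: effect on slope and correlation.** For an all-births correlation r, the slope of birth weight on body composition is multiplied by k/[1 − r²(1 − k)], and the correlation by the square root of that factor. With r = 0.2:

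| SD (g) | Mean (g) | k | Slope factor | Correlation factor | 0.2 becomes |
|---|---|---|---|---|---|
| 350 | 2795 | 0.138 | 0.143 | 0.378 | 0.076 |
| 400 | 2837 | 0.136 | 0.141 | 0.375 | 0.075 |
| 450 | 2879 | 0.129 | 0.134 | 0.365 | 0.073 |
| 500 | 2921 | 0.119 | 0.123 | 0.351 | 0.070 |
| 600 | 3005 | 0.098 | 0.101 | 0.319 | 0.064 |

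For small r the slope factor equals k, which runs from about 1/7 to 1/10 over this SD range. Letting the low birth weight share also vary from 15% to 30% widens k to 0.093–0.161.

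**Step 3: simulation.** With 4 million simulated births, SD 450 g and r = 0.2, the slope was 90.2 g per SD of body composition in all births and 12.2 g inside the window (ratio 0.135). The correlation factor was 0.370. The reverse slope, body composition on birth weight, hardly moved: 0.000445 against 0.000450 SD per gram.

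**Step 4: sensitivity to shape.** A lower tail heavier than the normal one leaves more variance in the window. As a rough bound, a flat density across the 750 g band has SD 750/√12 = 217 g. At a population SD of 450 g this gives (217/450)² = 0.23, or about one quarter.

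**Step 5: detectability.** Two-sided 5% power for a correlation is about Φ[√(n − 3) × atanh(r) − 1.96]. At SD 450 g:
- True r = 0.2 (0.073 in the window): 40% with 550 pairs and 35% with 468. Without truncation both exceed 99%.
- True r = 0.3 (0.112 in the window): 75% and 68%.
- True r = 0.5 (0.203 in the window): above 99% for both.

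**The case against.** The strongest reply is that the project concerns low-birth-weight infants throughout. If the intended target is infants of 1500 to 2250 g, the within-window slope is a description of that group and not a biased estimate. This stands as far as it goes: the bias exists only against an all-births target. But the plan does not state either target, and the title in Annexure 5 B carries no restriction, although some sibling titles do mention LBW infants or neonates.

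Four stronger readings are tempting and should be resisted.
- A reader might take a single factor, such as one eighth, as established. The birth-weight SD and shape are not in the documents, so only a conditional range can be given.
- A reader might apply the slope factor to every measure of association. The correlation falls only to about one third, and the slope of body composition on birth weight is essentially unchanged. The objective's wording does, however, point in the attenuated direction.
- A reader might conclude that even a strong relation would look like none. Step 5 does not support that. A true correlation of 0.5 would still be detected, though with a much smaller slope; it is modest correlations that would often be missed.
- A reader might add that body composition is measured after the birth weight it is meant to explain. The documents give no measurement time for body composition. Days 4 to 7 or later is an inference from sub-study enrolment, and the point is not relied on here.

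It is also fair that the item is optional and tentative. That limits its severity but does not remove the problem.

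**Conclusion.** The concern holds as a minor point. The objective and the paper select on their own outcome, and the plan neither handles this nor restricts the claim. Relative to all births, and under the stated normal model with 20% low birth weight and SD 350 to 600 g, the regression slope of birth weight on body composition is about one seventh to one tenth of its value and the correlation about one third. With a less thin lower tail the slope could be up to about one quarter. The direction and seriousness of the shrinkage survive these alternatives; the exact factor does not. The objective appears in neither the primary nor the secondary objectives, nor in the SAP, and the randomised comparisons are unaffected.

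**What to change.** Remove infant birth weight as an outcome from the third objective of Annexure 5 A and the sixth title of Annexure 5 B, keeping breast milk intake and linear growth.

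If birth weight is kept, state that the association is conditional on birth weight of 1500 to 2250 g and is not to be generalised to all births. A truncated-normal regression with limits 1500 and 2250 g may be added, but only as a sensitivity analysis with its distributional assumption declared. In the central case the window holds only about 8% of births (Z = 0.080), so that model would lean heavily on the assumed shape.

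The cost is the wording of one objective and one tentative title. Data collection, sample size and participant procedures do not change. The downside is that one optional secondary-data result is dropped or narrowed.
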